## Methods

### Study design

This prospective trial was designed as a single-center randomized, open-label, superiority clinical trial with patients allocated 1:1, to be conducted at the First Affiliated Hospital of Shantou University Medical College, Shantou, Guangdong, China. The protocol was designed according to the Standard Protocol Items: Recommendations for Interventional Trials (SPIRIT) 2013 Statement.

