### Sample size

Preliminary data indicates that acute aortic dissection is associated with an in-hospital mortality of 27.4% [18]. We predict that treatment with atorvastatin will reduce mortality to 12.4%, while no change will be seen in the control group, which will show a mortality of 27.4%. To obtain 90% power to demonstrate a statistically significant difference (two-sided test, alpha = 0.05) between the two treatments, we anticipate that 307 participants will need to be recruited with154 for the control group and 153 for the statin group. This corresponds to a hazard ratio of 0.4135. Given the possibility of exclusion or lost follow-ups, an increase of 20% will be required for the sample size, bringing the sample size to 192 per arm for a total of 384 participants to be enrolled. All calculations are done through PASS software (NCSS, America, version 11), using the log-rank test, Freedman method.

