### Safety and adverse events

The most common AEs related to the intake of atorvastatin are expected to be liver enzyme abnormalities, muscle pain, nausea, and diarrhea. Participants showing any adverse event will be treated appropriately by doctors, and the project will cover the cost of adverse events. Adverse reactions will be checked at every visit. For any AE that occurs, all details, including the time of occurrence, symptoms and signs, degree, duration, laboratory findings, treatment, outcomes, and causal relationship with the treatment, will be recorded in the CRF. Serious AEs will be reported to the Research Ethics Committee within 24 h, which will decide whether any additional measures should be taken. The total number of patients with AEs related to the study drug (certain, probable, possible) and the total number of patients with AEs leading to discontinuation of study treatment will be summarized.

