### Limitations

The limitations of this study should also be considered, including confirming that patients can diet normally before being formally included in the study, which may exclude critically ill patients whose deaths would occur within several hours of onset and would not be reported, thereby reducing the mortality rate reported for AAD. For surgical patients, preoperative fasting is often required, and patients in this group often need to wait until a normal diet is restored after surgery before they can be included in the study, which may also exclude critically ill patients whose deaths would occur before normal dieting is restored and would not be reported, thereby reducing the mortality rate reported for AAD. Considering the safety of atorvastatin, a low dose of 20 mg/day will be used in this study, and any possible effects may not be very significant. This is an exploratory study. If there is no significant positive effect at the end, but the results suggest it is safe and does not increase mortality, effectiveness may be observed by subsequently increasing the dose. We will explore the most appropriate dose in the next study. As atorvastatin is a tablet drug, we have sought several companies including Pfizer for suitable tablet placebo, while we failed to find out such placebo that are totally the same in color, shape, smell, and taste. So this is an open-label trial which may weaken its persuasiveness. However, if the results of this study are positive, it will provide evidence in reducing in-hospital mortality in patients with AAD, we will continue to carry out multicenter double-blind study to verify the results of this experiment.

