## Discussion

AAD confers poor prognosis if left unmanaged [22]. Currently, although surgical treatment can significantly reduce the mortality, the mortality remains high, which indicates other interventions are needed to further reduce the mortality rate. The 17-year trends in the presentation, diagnosis, and hospital outcomes of AAD from the IRAD were retrospectively reviewed by Linda et al. [2], who showed that besides angiotensin receptor blockers and beta-blockers used to treat AAD, statins are being used with increasing frequency.

Numerous studies indicate that statins have multiple beneficial actions on the cardiovascular system through improvement of endothelial dysfunction, inflammation, oxidative stress, and stabilization of atherosclerotic plaques [23]. Endothelial dysfunction has been recognized as an independent predictor of cardiovascular disease, and statins significantly ameliorate endothelial dysfunction [24, 25]. The reason why we choose atorvastatin is that atorvastatin is the most widely used statin and has been administered in a variety of settings, the incidence of AEs with atorvastatin 10–40 mg in patients of Asian origin is low, and compared with other statins, atorvastatin is safer and has greater beneficial effects on oxidative stress and endothelial function [26–28].

The objective of this trial is to assess the effect of statins on the mortality of AAD patients. If the results of our investigation are positive, this study will provide evidence regarding the value of statins as an intervention to decrease in-hospital mortality in patients with AAD. Also, if there is no significant positive effect at the end, but the results suggest it is safe and does not increase mortality, effectiveness may be observed by subsequently increasing the dose. We will explore the most appropriate dose in the next study.

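### The stated AE summaries compare the arms on little beyond liver dysfunction and death, and the foreseen no-harm reading of a null mortality result is not tied to its confidence interval

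*Protocol article*

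**What the plan says.** Study design (protocol article) describes a "single-center randomized, open-label, superiority clinical trial with patients allocated 1:1". Sample size builds on one contrast: "acute aortic dissection is associated with an in-hospital mortality of 27.4" per cent, and "We predict that treatment with atorvastatin will reduce mortality to 12.4" per cent. The stated aim is "To obtain 90% power to demonstrate a statistically significant difference (two-sided test, alpha = 0.05"). The statistical section gives a chi-square test for the binary primary outcome.

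Limitations then says what happens if that test is negative: "If there is no significant positive effect at the end, but the results suggest it is safe and does not increase mortality", effectiveness may be looked at in a later study. Discussion repeats it: "if there is no significant positive effect at the end, but the results suggest it is safe and does not increase mortality". Just before the first of these, Limitations also says "This is an exploratory study". No margin, confidence-interval criterion or other rule defines the no-increase condition.

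On AEs, Safety and adverse events names two totals. One is "The total number of patients with AEs related to the study drug (certain, probable, possible"). The other is patients whose AEs led them to stop study treatment. Interventions says that controls take no statin, and Limitations explains that no matching placebo could be found. Blinding says that investigators and assessors know the allocation. Follow-up has AEs recorded for each subject. Outcome measurements makes liver dysfunction the secondary outcome, from ALT and AST at days 7 and 13.

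**The concern.** The protocol states in advance a conclusion about absence of harm and a use for it, so the planned evidence should be able to carry that conclusion.

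For safety, the two named AE totals do little. A control patient has no study drug for an AE to be related to and no study treatment to stop. A control who started a statin might in principle contribute, so the counts are confined to the statin arm in effect rather than by definition. Relatedness is also judged by people who know the allocation. Of the four AE types that the protocol itself expects, only liver enzyme abnormality has a stated route to a between-arm comparison. Muscle pain, nausea and diarrhoea have none.

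For mortality, a superiority test that fails to reject says only that no difference was demonstrated. Whether an increase has been ruled out depends on the width of the confidence interval, and the protocol does not link its statement to that. At stake is whether a result compatible with several excess deaths per 100 patients could be described as showing no increase and then used to motivate the next trial.

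**Working it through.** **1. The plan's own sample size.** Inputs from Sample size: 27.4% v 12.4%, two-sided 0.05, 90% power, log-rank test by the Freedman method, 20% loss.
- HR = ln(1 − 0.124) / ln(1 − 0.274) = 0.4135.
- Events = (1.960 + 1.282)² × ((1 + 0.4135)/(1 − 0.4135))² = 61.02.
- N = 61.02 / ((0.274 + 0.124)/2) = 61.02 / 0.199 = 306.6, so 307.
- Enrolled = 307 / 0.8 = 383.75, so 384.

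All stated figures reproduce. The size is sound for its stated purpose, a 15-point reduction.

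**2. What a null mortality result would exclude.** Half-width of the 95% CI for the risk difference at equal mortality p with n per arm: 1.96 × √(2p(1 − p)/n). For example, 1.96 × √(2 × 0.274 × 0.726/192) = 0.089.

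| Mortality in both arms | 192 per arm (no loss) | 153.5 per arm (307 evaluable) |
|---|---|---|
| 27.4% (protocol) | ±8.9 points | ±10.0 points |
| 20% (assumed) | ±8.0 | ±8.9 |
| 15% (assumed) | ±7.1 | ±8.0 |

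The lower rates are assumptions. They are included because Limitations expects the enrolment rules to lower the observed mortality.

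**3. How often a true 5-point increase would go unflagged.** Take 27.4% v 32.4%, and read the phrase as no significant increase. With 192 per arm and average rate 0.299:
- z = [0.05 − 1.96 × √(2 × 0.299 × 0.701/192)] / √((0.274 × 0.726 + 0.324 × 0.676)/192) = −0.89.
- Power = 0.186, so the miss probability is about 0.81.

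Exact enumeration of the chi-square test over all pairs of binomial counts gives 0.813 with 192 per arm and 0.841 with 154 and 153. At assumed rates with 192 per arm it gives 0.748 (15% v 20%) and 0.786 (20% v 25%).

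**4. The same question under another reading.** Suppose the phrase means that observed statin mortality is no higher than control. Summing the same binomial probabilities over the pairs that meet this condition gives, with 192 per arm, 11% (15% v 20%) and 13% (20% v 25%). At 27.4% v 32.4% it gives about 15% (192 per arm) to 16% (154 and 153). The answer therefore depends heavily on a definition that the text does not supply.

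**5. Chance of excluding an increase if there is truly none.** The protocol gives no margin, so 3, 5 and 10 points are assumptions. With SE = √(2 × 0.274 × 0.726/n), the power is Φ(margin/SE − 1.96). Results for 154 and 192 per arm:
- 10 points: 50% and 59%.
- 5 points: 16% and 19%.
- 3 points: 8.5% and 9.7%.

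**6. The safety comparison that does exist.** Liver dysfunction is measured in both arms. The documents give no expected rates. At an assumed 2% in each arm, the 95% half-width is 2.8 points (192 per arm) to 3.1 points (154). For an assumed 1% v 3%, power is 29% and 24%. This is imprecise, but it is a comparison between randomised arms.

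**The case against.** A reader might infer that the safety conclusion would have no between-arm support at all. The documents do not support that. Liver dysfunction is the only named secondary outcome, ALT and AST are scheduled for all participants at baseline and days 7 and 13, and categorical data get a chi-square test. All-cause death is compared as well. The monitoring committee also reviews all AEs at 25%, 50% and 75% of enrolment, though that is oversight during the trial and not a stated final comparison.

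It can further be said that naming two totals does not rule out others, and that an all-AE table by arm is routine content for the analysis plan promised before database lock. That is fair. The point is therefore limited to the summaries this document does fix, which are the ones least able to compare the arms.

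On mortality, a reader might infer that the protocol derives absence of harm from the non-significant test. It does not say so. The sentence sets a separate condition that the results suggest no increase. It is tentative, sits beside a statement that the study is exploratory, and leads only to further research. All of that stands, but it leaves the condition undefined, and cautious wording does not narrow a confidence interval.

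Finally, a reader might infer that a modestly harmful drug would usually pass. That follows only if the phrase means no significant increase. If it means observed mortality no higher than control, a true 5-point increase would pass only about 11–16% of the time.

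**Conclusion.** The concern holds in limited form. The two AE totals that the protocol names are in effect empty in the control arm. Beyond liver dysfunction and death, the stated summaries therefore offer no between-arm safety comparison, although the data for one are collected. Separately, the no-increase statement is not tied to precision. At 27.4% mortality, an observed difference of zero leaves increases of up to about 8.9 to 10.0 points unexcluded, or 7.1 to 8.0 points at an assumed 15%.

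The 81–84% miss rate for a 5-point rise from 27.4% is conditional on one reading of an undefined phrase and should be quoted only with that condition. The 192-per-arm figures assume no loss. The 15% and 20% mortalities, the margins and the liver rates are assumptions. Neither the sample size nor the primary superiority test is at fault here, and no comment is made on any later dose.

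**What to change.** 1. In Safety and adverse events, add a table of all AEs and all serious AEs by randomised arm, regardless of attribution, with risk differences and 95% CIs, placed alongside the liver outcome. Keep the drug-related counts as a supplement.
2. In Limitations and Discussion, replace the undefined condition. Report the 95% CI for the mortality difference, and state no increase only if its upper limit excludes an increase fixed in advance. Otherwise call the result inconclusive on harm.

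The cost is one extra table from data already recorded and a few changed sentences. The investigators must choose and justify the excluded increase before they see results. The real downside is that, at this sample size, a null result will probably have to be labelled inconclusive on harm. That would describe accurately what the trial can show.

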## Discussion

AAD confers poor prognosis if left unmanaged [22]. Currently, although surgical treatment can significantly reduce the mortality, the mortality remains high, which indicates other interventions are needed to further reduce the mortality rate. The 17-year trends in the presentation, diagnosis, and hospital outcomes of AAD from the IRAD were retrospectively reviewed by Linda et al. [2], who showed that besides angiotensin receptor blockers and beta-blockers used to treat AAD, statins are being used with increasing frequency.

Numerous studies indicate that statins have multiple beneficial actions on the cardiovascular system through improvement of endothelial dysfunction, inflammation, oxidative stress, and stabilization of atherosclerotic plaques [23]. Endothelial dysfunction has been recognized as an independent predictor of cardiovascular disease, and statins significantly ameliorate endothelial dysfunction [24, 25]. The reason why we choose atorvastatin is that atorvastatin is the most widely used statin and has been administered in a variety of settings, the incidence of AEs with atorvastatin 10–40 mg in patients of Asian origin is low, and compared with other statins, atorvastatin is safer and has greater beneficial effects on oxidative stress and endothelial function [26–28].

The objective of this trial is to assess the effect of statins on the mortality of AAD patients. If the results of our investigation are positive, this study will provide evidence regarding the value of statins as an intervention to decrease in-hospital mortality in patients with AAD. Also, if there is no significant positive effect at the end, but the results suggest it is safe and does not increase mortality, effectiveness may be observed by subsequently increasing the dose. We will explore the most appropriate dose in the next study.

## Trial status

The version of this protocol is 2.0 (date 20201225). It is currently recruiting patients.

## Data Availability

The project owner will have access to the final trial dataset. The trial data will be made public and manuscript(s) will be published in a peer review clinical journal regardless of whether the results of the trial are positive, negative or inconclusive.

## Abbreviations

AAD: Acute aortic dissection
ABAD: Acute type B aortic dissection
AD: Aortic dissection
ALT: Alanine aminotransferase
AST: Aspartate aminotransferase
CONSORT: Consolidated Standards of Reporting Trials
CRF: Case report forms
CTA: Computed tomography angiography
IRAD: International Registry of Acute Aortic Dissection
IRB: Institutional review board
ITT: Intention-to-treat
LDL-C: Low-density lipoprotein cholesterol
RCT: Randomized controlled trial
TEAE: Treatment-emergent adverse events
